**8.5 Assessment of the Relationship between AEs and the Investigational Drug**

Based on whether there is a reasonable temporal sequence between the occurrence of AE and the use of the study drug, the type of drug reaction, and whether the reaction lessens, disappears, or reappears after discontinuation of the drug, the association between the AEs and the study drug is classified as definitely related, probably related, possibly related, possibly unrelated, and definitely unrelated. The first three categories are considered possibly related to the study drug, and evaluated as adverse drug reactions.

Details of the relationship between AE and the study drug are as follows:

- Definitely related: There is evidence of the use of the study drug, and the occurrence of the AE has a reasonable temporal sequence with the use of the study drug. The AE is more reasonably explained by the study drug than by other causes. Positive reaction upon discontinuation, positive reaction upon re-administration (if feasible).
- Probably related: There is evidence of the use of the study drug, and the occurrence of the AE has a reasonable temporal sequence with the use of the study drug. The AE is more reasonably explained by the study drug than by other causes. Positive reaction upon discontinuation.
- Possibly related: There is evidence of the use of the study drug, and the occurrence of the AE has a reasonable temporal relation with the use of the study drug. The AE can also be explained by other causes. Positive reaction upon discontinuation.
- Possibly unrelated: There is evidence of the use of the study drug, but the AE is more reasonably explained by other causes. Negative or unclear reaction upon discontinuation.
- Definitely unrelated: The study drug was not used, or there is no temporal relationship between the use of the study drug and the occurrence of the AE, or there is a clear other cause of the AE.

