**8 Safety assessment**

**8.1 Definitions**

- AE: An AE is any unfavourable medical occurrence in a participant that may present as symptoms, signs, illness, or laboratory findings after taking the trial medication. These events are not necessarily causally related to the trial medication.
- SAE: A SAE is any adverse medical event that occurs after taking the trial medication and results in death, life-threatening situations, permanent or significant disability or incapacity, requires hospitalization or prolongation of existing hospital stay, or causes congenital anomalies or birth defects.
- Suspected Unexpected Serious Adverse Reaction (SUSAR): This refers to an adverse reaction that is both unexpected and serious, where the nature and severity of the clinical presentation exceed what is described in the drug's Investigator's Brochure, the marketed product's package insert, or the product characteristics summary, and where the reaction is not anticipated based on the current knowledge.
- Drug Adverse Reaction: This term refers to any harmful or undesired effect in clinical trials that is possibly related to the trial medication. There is at least a reasonable possibility of a causal relationship between the trial medication and the AE, meaning that the relationship cannot be ruled out.

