**8.4 Severity grading of AEs**

Mild: Minor self-perceived symptoms that are tolerable, do not affect daily activities, are transient, resolve on their own during continued medication use, and require no treatment.

Moderate: Symptoms are noticeable, affect the subject's daily activities, persist for a longer duration, and may resolve on their own or after symptomatic treatment. They may interfere with the use of the study medication, possibly necessitating a reduction in dosage or discontinuation of the drug.

Severe: The subject’s bodily functions are impaired, losing the ability to work or live normally, with symptoms persisting for a long duration, requiring discontinuation of the medication and appropriate management before resolution.

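### Section 8.5 lists a positive response to stopping the drug in every category that counts as an adverse drug reaction, so some suspected reactions have no valid code, and this contradicts section 8.1

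*Protocol*

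**What the plan says.** Section 8.5 of the protocol sets out five grades, from definitely related to definitely unrelated, and then fixes which of them count: "The first three categories are considered possibly related to the study drug, and evaluated as adverse drug reactions".

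The discontinuation criterion appears in each of those three:

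- Definitely related: "Positive reaction upon discontinuation, positive reaction upon re-administration (if feasible" (the feasibility proviso is attached to re-administration).
- Probably related: "The AE is more reasonably explained by the study drug than by other causes. Positive reaction upon discontinuation".
- Possibly related: "The AE can also be explained by other causes. Positive reaction upon discontinuation".

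A response that is not positive is mentioned only under *possibly unrelated*: "but the AE is more reasonably explained by other causes. Negative or unclear reaction upon discontinuation".

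Two other sections bear on this. Section 8.4 describes mild events as ones that "resolve on their own during continued medication use, and require no treatment". Section 8.1 defines a drug adverse reaction by a reasonable possibility of a causal link, "meaning that the relationship cannot be ruled out", and sets no condition on what happens when the drug is stopped.

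**The concern.** A response to discontinuation can be observed only if the event is still present when the drug stops and is capable of improving. Many suspected reactions do not meet those conditions. The drafters foresaw that re-administration may not be possible, but made no similar allowance for a stopping response that cannot be assessed.

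Safety is one of the two primary objectives (section 2), L-oxiracetam is not marketed anywhere (section 1.4), and relation to the study drug must be recorded for every adverse event (section 8.3.2). The reactions listed in section 8.2, such as itching, nausea and anxiety, can plausibly be mild and short-lived, which is the kind of event the wording handles badly. Site physicians in 74 centers would have to follow the text literally or improvise around it. A causality grade that was never properly assigned cannot be recovered later by an analysis plan.

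**Working it through.** There is no figure to reproduce. The check sets the five grades side by side and then runs each type of event through them.

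| Grade in 8.5 | Drug against other causes | Response to stopping | Allowance if not assessable | Counts as reaction |
|---|---|---|---|---|
| Definitely related | drug explains better | positive | none | yes |
| Probably related | drug explains better | positive | none | yes |
| Possibly related | other causes also fit | positive | none | yes |
| Possibly unrelated | other causes explain better | negative or unclear | – | no |
| Definitely unrelated | drug not used, no temporal link, or a clear other cause | not mentioned | – | no |

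So 3 of 5 grades count as reactions, 3 of those 3 list a positive response, and 0 of 3 allow for one that is missing or unclear.

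**Event that resolves on drug.** By the section 8.4 description, a mild event ends while dosing continues. There is then no response to stopping to observe, so none of the three related grades is met.

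**Fatal or irreversible event.** Section 8.1 includes death and permanent disability among serious events. Neither can lessen or disappear after the drug is stopped, so again none is met.

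**Event that begins after the last dose.** Dosing lasts 14 days (section 5.12), follow-up lasts 90 days (section 5.6), and the Trial Schedule marks adverse event recording at Days 30, 60 and 90. Such an event has no drug left to withdraw. This case is weaker than the other two: an event that clears up might loosely be said to have disappeared after discontinuation, and many late onsets would fail the separate requirement of a reasonable temporal relation.

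**Where these events go instead.** *Possibly unrelated* requires another cause to be the better explanation. If the drug is the better explanation, that grade is not met. *Definitely unrelated* is not met either when the drug was given, the timing is reasonable and no other cause is clear. The event then fits none of the five grades. The same gap opens when another cause is possible but not the better one, and the response to stopping is unclear.

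**Against section 8.1.** Each of these events can have a relationship that cannot be excluded, so section 8.1 calls it a reaction while section 8.5 offers no grade that does so.

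**Illustration.** Nausea that starts on Day 3 and settles on Day 5 under continued dosing meets no related grade. The same nausea starting on Day 13 and fading after Day 14 can meet one. The two codings differ because of when dosing stopped, not because of any evidence about cause.

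**The case against.** The strongest reply is that section 8.5 opens by naming several considerations (timing, type of reaction, course after stopping), so its bullets describe typical cases for medical judgement and are not a checklist. The section 8.4 description of mild can be read the same way, and section 8.1 remains available as the general definition. This is a fair account of how an experienced physician might proceed. It does not rescue the text: if physicians depart from the bullets, each site substitutes its own unrecorded rule, and the conflict with section 8.1 remains.

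Three further objections stand and limit the point:

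- **Serious events.** Section 8.7.2 requires every serious event to be reported to the sponsor whether or not it is thought related, and the sponsor must assess the relationship itself. A reader might infer that a fatal unexpected event would escape reporting as a suspected unexpected serious adverse reaction. The document does not support that. The site's grade is not the only gate, so the path is at most weakened.
- **Comparison with placebo.** The safety endpoint in section 7.2 is adverse events, not adverse reactions, and section 14 names no between-arm comparison of reactions. A reader might infer that the main safety comparison is biased towards no difference. It is not, because all-cause counts do not depend on causality grading. Only a tabulation of related events would be affected.
- **Events after Day 14.** An event that starts on treatment and subsides after the last dose can show a positive response. Only onset after the last dose is in question.

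**Conclusion.** The defect holds as a contradiction between sections 8.5 and 8.1 and as a gap in the section 8.5 grades. Followed as written, section 8.5 leaves some suspected reactions without a valid code, and adverse drug reactions are likely to be under-counted or coded differently from site to site.

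The size cannot be estimated: the documents do not say how many events would be mild, fatal, irreversible or of late onset. A reader might infer that all mild and all fatal events can never count as reactions, or that fatal events are moved wholesale to *possibly unrelated*. The first goes too far because it treats a literal reading of section 8.5 as if section 8.1 did not exist. The second fails because *possibly unrelated* needs a better alternative cause; a death best explained by the drug lands in no grade at all.

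The conclusion assumes that each listed element of a grade is meant to be met. If the elements are only descriptors, the effect is inconsistency between sites rather than systematic loss. Either way, this should be corrected in the protocol, because the grades are assigned at the sites under its wording.

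**What to change.** Reconcile section 8.5 with section 8.1 as follows:

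- *Possibly related*: keep the reasonable temporal relation and the possibility of other causes; accept a response to discontinuation that is positive, unclear or not applicable.
- *Definitely related* and *probably related*: accept not applicable where the event resolved on drug, is irreversible or fatal, or began after the last dose.
- *Possibly unrelated*: keep for events better explained by another cause.

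The redraft should also say where a negative response belongs when no other cause is the better explanation, so that every event has a grade.

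The cost is a few lines of protocol wording and an update to the eCRF completion guide. The downside is a somewhat higher reported adverse-reaction rate in all arms. No dose, visit or treatment rule changes.

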**8.6 Follow-up of Adverse Event Outcomes**

It is necessary to follow up on AEs that have not resolved by the end of the study or are still unresolved, until one of the following occurs:

- The event is alleviated;
- The event stabilizes;
- If baseline values are acceptable, the event returns to baseline levels;
- When no further information can be obtained (e.g., if the subject or their healthcare provider refuses to provide further information, or if a subject is proven to be lost to follow-up despite efforts).

Follow-up methods can vary based on the severity of the adverse reaction, including hospitalization, outpatient visits, home visits, phone calls, and correspondence.

**8.7 Serious AEs**

8.7.1 Management of SAEs

- When considered a SAE, the attending physician must notify the principal investigator or other responsible physician to attend. If the condition is critical, resuscitation should begin while notifying the project leader; if necessary, the investigational drug should be immediately discontinued;
- If identified as a SAE, appropriate clinical emergency treatment measures should be taken immediately based on clinical symptoms. If caused by a drug overdose leading to severe toxicity, the researcher should decide on measures to accelerate drug excretion to stabilize vital signs as much as possible, with cardiac monitoring if necessary, and consult with relevant departments for assistance if needed.
- If an outpatient is judged to have a SAE and cannot come to the clinic, it is advised that the subject return to the hospital or go to a local hospital for treatment while immediately notifying the project leader to get further handling advice. If treated at a local hospital, contact should be established with the attending doctor to understand the specifics and provide treatment recommendations. If necessary, log in to the IWRS system to initiate the unblinding process.

8.7.2 Reporting of SAEs

Any SAEs occurring during the trial, whether related to the investigational drug or not, must be promptly treated by the researcher and immediately reported in writing to the sponsor, followed by a detailed written follow-up report. SAE reports and follow-up reports should use the subject's identification code from the clinical trial, not the subject's real name, national ID number, or address.

Upon receiving any safety-related information from any source, the sponsor must immediately analyze and assess it, including the severity, relationship to the investigational drug, and whether it was an expected event. The sponsor should promptly report any suspected and unexpected serious adverse reactions to all investigators and clinical trial sites involved, as well as to ethics committees; the sponsor should also report these reactions to the drug regulatory authority and health authorities.

Researchers, upon receiving relevant safety information from the sponsor about the clinical trial, must promptly acknowledge and review it, consider adjusting treatment for the subject, if necessary, communicate with the subject at the earliest opportunity if needed, and report any suspected and unexpected serious adverse reactions provided by the sponsor to the ethics committee.

For reports involving death events, researchers should provide other required information to the sponsor and ethics committee, such as autopsy reports and final medical reports.

8.7.3 Pregnancy

If a subject becomes pregnant during the clinical trial, they must immediately discontinue the medication. The investigator must report the pregnancy to the sponsor within 24 hours of becoming aware and promptly inform the ethics committee. The investigator is responsible for following up on the pregnancy outcome until the termination of the pregnancy or one month after delivery, and must report the results to the sponsor.

8.7.4 Hospitalization

AEs that lead to hospitalization or extend the duration of hospitalization during a clinical trial should be considered SAEs. Any initial admission to a medical facility, even if it is shorter than 24 hours, meets this criterion. Exclusions from hospitalization include:

- Rehabilitation facilities
- Sanatoriums
- Routine emergency room admissions
- Day surgeries (such as outpatient/ day/ non-inpatient surgeries)

Hospital treatments or extended hospital stays that are unrelated to the worsening of an AE are not considered SAE. Examples include:

- Admission due to a pre-existing condition without any new AEs or worsening of the condition (e.g., for ongoing lab abnormalities that have been present since before the trial).
- Hospital stays for administrative reasons (such as annual routine check-ups).
- Hospitalizations specified by the clinical trial protocol (e.g., procedures required by the trial protocol).
- Elective hospitalizations unrelated to the worsening of an AE (such as elective cosmetic surgery).
- Scheduled treatments or surgical procedures that should be documented in the entire trial protocol and/ or the subject's baseline information.
- Hospital admissions solely for the use of blood products.

**9 Data Management**

This study utilizes an eCRF for the collection and management of research data, maintaining a complete audit trail to ensure the traceability of clinical trial data. The data management process must comply with Good Clinical Practice (GCP) standards to ensure the authenticity, integrity, and accuracy of clinical trial data.

**9.1 Developing a Data Management Plan**

Data managers, adhering to GCP guidelines and relevant clinical trial particulars, develop a data management plan. This plan records, describes, and defines the various tasks in data management, guiding the entire process. It should include aspects such as database creation, data entry, data verification, query management, medical coding, and database lock, and it should specify key timelines and clearly define the responsibilities of related personnel.

**9.2 Database Creation**

Database designers are responsible for creating the project database and conducting tests to ensure its accuracy and correctness.

**9.3 Data Entry**

Researchers at the study center or Clinical Research Coordinators (CRCs), following the "eCRF Filling Guide," perform data entry. Before data entry begins, the sponsor must train the relevant personnel at the study center to understand the content of the eCRF, familiarize themselves with the database structure and functionality, and recognize issues to avoid during entry. During the data entry process, researchers or CRCs can contact the data department at any time to resolve any questions encountered.

**9.4 Data Verification**

Data managers, following the Data Verification Plan, audit trial data. Main verification areas include missing data, logical issues, time windows, inclusion/ exclusion criteria, medication adherence, and consistency checks. Methods of data verification include eCRF logical checks, programmatic checks, manual reviews, and medical reviews. If data entering into the eCRF system does not meet logical requirements, the eCRF system or relevant personnel can issue queries that the study center must respond to. If the response is satisfactory, the query is closed. If the query remains unresolved, or if new queries arise from the updates made to the database following previous queries, the study center must provide new responses. This process repeats until all data in the database are confirmed as correct.

**9.5 Database Lock**

After drafting a data audit report based on the trial protocol and data review standards, the project manager organizes a data review meeting. The sponsor, principal investigator, statisticians, and data managers attend this meeting to review the data and partition the analysis datasets. Once the data manager completes the data lock inventory and following the database locking procedure, the statistician, sponsor, and principal investigator sign the database lock approval document, and the data manager then executes the database lock. If there is concrete evidence that unlocking the database is necessary after it has been locked, the researcher and relevant personnel must sign a database unlock document.

**9.6 Data document preservation and data transfer**

Data administrators should save data management-related documents as required, and hand over the locked database and related information to statistical analysts for statistical analysis.

**10 Sample size calculation**

Before conducting this study, we conducted a pilot trial: The change values of the total scores on the LOTCA scale at 90 days post-drug cessation compared to baseline for L-oxiracetam and oxiracetam were 26.0 ± 11.8 and 22.8 ± 10.0, respectively. The combined standard deviation (SD) for both groups was 11.0, with α set at 0.05 and 1-β at 0.8. Employing an optimal design with a sample ratio of 1:1, PASS software calculated a sample size of 190 cases for each group.

The change values of the total scores on the LOTCA scale at 90 days post-drug cessation compared to baseline for the L-oxiracetam group and the placebo group were 26.0 ± 11.8 and 20.0 ± 11.4, respectively. The combined SD for both groups was 11.6, with α set at 0.05 and 1-β at 0.8. Employing an optimal design with a sample ratio of 2:1, PASS software calculated a sample size of 204 cases for the L-oxiracetam group and 102 cases for the placebo group.

Considering potential dropouts, we increased the sample size by 15%. Therefore, the sample sizes for the L-oxiracetam group, oxiracetam group, and placebo group were set at 236, 236, and 118, respectively.

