**14 Statistical analysis plan**

SAS 9.4 was used for data analysis independently conducted by a biostatistician unaware of the allocation. Continuous variables will be presented as mean ± SD with a 95% CI for normal distribution and as median (range) for abnormal distribution. Categorical variables will be expressed by numbers and percentages. All hypothesis tests were two-sided with α = 0.05. A P-value ≤ 0.05 indicated statistical significance.

The analysis for the primary outcome was conducted using analysis of covariance (ANCOVA). The least squares means of change from baseline at 3 months in LOTCA scores, as well as the mean differences between groups (L-oxiracetam vs. oxiracetam/ Placebo) and 95% CIs were estimated. Cohen’s d and 95% CI was used to calculate the effect size. For the secondary continuous efficacy outcomes, mean differences with corresponding 95% CIs were also analyzed using ANCOVA. For categorical outcomes of GOS-E, the rate differences and 95% CIs between groups were estimated using the approximate normality method and statistically tested with Fisher's exact probability test. All models were adjusted for age, sex, education, and TBI severity at baseline. Stratified analyses were performed to explore the efficacy of the L-oxiracetam intervention on cognitive function in patients with different age (< 60 vs. 60 + years), sex (male vs. female), education (none vs. Primary vs. Secondary school or Higher), and TBI severity (mild vs. moderate). Moreover, multiplicative interactions were tested by including a cross-product item in the model for the intervention group with age, sex, education, or TBI severity.

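### The placebo-comparison sample size of 204:102 does not follow from its stated inputs, which need 90:45; the figure sets enrolment and oversizes the trial without costing power

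*Protocol*

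**What the plan says.** Section 10 of the Protocol sizes two comparisons from pilot results for the change in LOTCA total score at 90 days after drug cessation. The Synopsis (Target Sample Size) repeats the calculation.

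- **Against placebo.** The changes "for the L-oxiracetam group and the placebo group were 26.0 ± 11.8 and 20.0 ± 11.4, respectively". The next sentence reads "The combined SD for both groups was 11.6, with α set at 0.05 and 1-β at 0.8". The allocation is given as "Employing an optimal design with a sample ratio of 2:1", and the result as "PASS software calculated a sample size of 204 cases for the L-oxiracetam group and 102 cases for the placebo group".
- **Against oxiracetam.** The changes "for L-oxiracetam and oxiracetam were 26.0 ± 11.8 and 22.8 ± 10.0, respectively". On the pooled SD and the error rates the text has: "for both groups was 11.0, with α set at 0.05 and 1-β at 0.8". With 1:1 allocation the result is 190 per group.
- **Enrolment.** A 15% increase for dropout leads to 236, 236 and 118.

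Section 10 does not say whether the tests are one- or two-sided. Section 14 does: "All hypothesis tests were two-sided with α = 0.05". Neither section states a superiority margin, an alpha split or a power above 0.8 for the placebo comparison.

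**The concern.** The placebo comparison assumes nearly twice the difference of the oxiracetam comparison (6.0 against 3.2 points) with a similar SD (11.6 against 11.0). Even allowing for 2:1 allocation it should need far fewer patients, yet its L-oxiracetam arm comes out larger (204 against 190).

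Two things are at stake. The stated power for one of the two comparisons that Section 14 names for the primary outcome does not match the stated sample size. And because 204 exceeds 190, a figure that cannot be reproduced is the one that fixes how many patients are randomised. A reader who tries to verify the enrolment basis from the Protocol will fail.

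**Working it through.** **Inputs for the placebo comparison.** Section 10: difference 26.0 − 20.0 = 6.0; SD 11.6 (the root mean square of 11.8 and 11.4 is 11.60, so this figure is sound); α 0.05; power 0.80; ratio 2:1. Section 14: two-sided.

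**1. Check the method on the line that should reproduce.** For the oxiracetam comparison, with difference 3.2, SD 11.0 and 1:1 allocation:

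n per arm = 2 × (1.960 + 0.842)² × 11.0² / 3.2² = 2 × 7.849 × 121 / 10.24 = 185.5, so 186.

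The noncentral t gives 187. The Protocol's 190 is within 2% to 3%, so an ordinary two-sample calculation accounts for that line.

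**2. Apply the same method to the placebo line.** With L-oxiracetam : placebo = 2:1, the variance factor per placebo patient is 1 + 1/2 = 1.5:

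n placebo = 1.5 × 7.849 × 11.6² / 6.0² = 1.5 × 7.849 × 134.56 / 36 = 44.006, so 45.

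The noncentral t also gives 45. Power is 0.794 at 88:44 and 0.803 at 90:45. The requirement is therefore 90:45, and the stated 204:102 is 102/45 = 2.27 times as large.

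**3. Power at the stated size.** At 204:102 with the stated inputs, power is 98.9%, against the 80% target.

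**4. What 204:102 would correspond to.** For 80% power at that size, the difference would have to be about 3.95 points or the SD about 17.6. Neither is stated.

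**5. Try other inputs.** Difference 6.0, SD 11.6, 2:1, noncentral t:

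| Variant | L-oxiracetam : placebo |
|---|---|
| One-sided 0.05, 80% power | 72:36 |
| Two-sided 0.025, 80% power | 110:55 |
| Two-sided 0.0167, 80% power | 120:60 |
| Two-sided 0.01, 80% power | 134:67 |
| Two-sided 0.05, 90% power | 120:60 |
| Two-sided 0.05, 99% power | 208:104 |
| Two-sided 0.01, 95% power | 202:101 |
| Two-sided 0.05, 80% power, 2-point superiority margin | 200:100 |

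Only the last three come near 204:102. None matches it exactly, and each needs an input that the Protocol does not state or that contradicts the printed α or power.

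**6. Effect on enrolment.**

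- From the placebo line: 102 × 1.15 = 117.3, rounded up to 118; 2 × 118 = 236. Total 236 + 236 + 118 = 590.
- From the oxiracetam line under 2:2:1: 190:190:95. Then 190 × 1.15 = 218.5, so 219; 95 × 1.15 = 109.25, so 110. Total 219 + 219 + 110 = 548.
- Difference: 590 − 548 = 42 patients.

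**7. Power delivered by the planned enrolment.** After 15% loss, 236 × 0.85 = 200.6 and 118 × 0.85 = 100.3, so about 200/200/100 are evaluable. Power is then 98.8% against placebo (6.0 points, SD 11.6) and 82.7% against oxiracetam (3.2 points, SD 11.0).

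**The case against.** The strongest reply is that nothing is lost. The 80% figure is a planning target, and both comparisons exceed it. The 2.27-fold ratio applies to one intermediate figure. Because allocation is fixed at 2:2:1, 190 per active arm already brings 95 placebo patients, and power against placebo at 190:95 is 98.4%. The practical excess before dropout is therefore 102 against 95 placebo patients, not 102 against 45. Type I error and the planned ANCOVA are untouched. All of this stands, and it limits the seriousness of the point. It does not make the printed calculation correct.

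A reader might go further and infer that a superiority margin of about 2 points was used and then left out of the analysis, so that a significant difference from zero would not support the claim for which the trial was sized. The documents do not support that. No margin is mentioned, a 2-point margin gives 200:100 rather than 204:102, and two other unstated inputs come about as close. The margin is one conjecture among several.

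A further fair objection is that replacing 204:102 with 90:45 and stopping there would leave 236/236/118 without a derivation, since 190 × 1.15 leads to 219. The correction has to deal with this as well.

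**Conclusion.** The point holds as an error in a stated sample size and its stated power. The printed inputs need 90:45; the Protocol gives 204:102, at which power is about 99%. The same line determines the planned 590, about 42 more (8%) than the 548 that the oxiracetam comparison would require under the Protocol's own dropout rule.

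The consequence is moderate. The trial is oversized relative to its stated basis, no power is lost, and the validity of the planned tests is not affected. What fails is the reproducibility of the enrolment justification.

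The result rests on a two-sample comparison of means with the Protocol's own difference, SD, α, power and ratio, and on two-sidedness taken from Section 14. It does not depend on the choice between normal and t formulas. A one-sided test would lower the requirement and widen the gap.

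**What to change.** Leave enrolment as it is, and amend Section 10 and the Synopsis in one of two ways.

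1. **State the input actually entered in PASS** that produced 204:102. Only if it was a superiority margin, carry that margin into the hypothesis in Section 14.
2. **Correct the line.** For example: *For a 6.0-point difference (SD 11.6, two-sided α 0.05, 2:1 allocation), 90 L-oxiracetam and 45 placebo patients give 80% power. The comparison with oxiracetam, at 190 per arm, is the limiting one. Enrolment is set at 236/236/118. With 15% dropout, about 200/200/100 evaluable patients give about 99% power against placebo (6.0 points, SD 11.6) and about 83% against oxiracetam (3.2 points, SD 11.0).*

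The second route, and the first where the input is not a margin, costs wording in two places and changes no patients or procedures. If a margin was used, the cost is higher, because the primary hypothesis against placebo in Section 14 also changes.
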